# Treating impulsivity with probiotics in adults (PROBIA): study protocol of a multicenter, double-blind, randomized, placebo-controlled trial

**DOI:** 10.1186/s13063-019-4040-x

**Published:** 2020-02-11

**Keywords:** Impulsivity, Compulsivity, Aggression, Microbiome, Probiotics, Synbiotics, ADHD, Borderline personality disorder, Nutrition

## Abstract

**Background:**

Impulsivity and compulsivity are related to emotional and social maladjustment and often underlie psychiatric disorders. Recently, alterations in microbiota composition have been shown to have implications for brain development and social behavior via the microbiota–gut–brain axis. However, the exact mechanisms are not fully identified. Recent evidence suggests the modulatory effect of synbiotics on gut microbiota and the contribution of these agents in ameliorating symptoms of many psychiatric diseases. To date, no randomized controlled trial has been performed to establish the feasibility and efficacy of this intervention targeting the reduction of impulsivity and compulsivity. We hypothesize that supplementation with synbiotics may be an effective treatment in adults with high levels of impulsivity and/or compulsivity.

**Methods/design:**

This is a prospective, multicenter, double-blind, randomized controlled trial with two arms: treatment with a synbiotic formula versus placebo treatment. The primary outcome is the response rate at the end of the placebo-controlled phase (response defined as a Clinical Global Impression–Improvement Scale score of 1 or 2 = very much improved or much improved, plus a reduction in the Affective Reactivity Index total score of at least 30% compared with baseline). A total of 180 participants with highly impulsive behavior and a diagnosis of attention deficit/hyperactivity disorder (ADHD) and/or borderline personality disorder, aged 18–65 years old, will be screened at three study centers. Secondary outcome measures, including changes in general psychopathology, ADHD symptoms, neurocognitive function, somatic parameters, physical activity, nutritional intake, and health-related quality of life, will be explored at assessments before, during, and at the end of the intervention. The effect of the intervention on genetics, microbiota, and several blood biomarkers will also be assessed. Gastrointestinal symptoms and somatic complaints will additionally be explored at 1-week follow-up.

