Recruitment began on 22 February 2019 and will have a duration of 2 years. A total of 180 participants (60 subjects per site) will be recruited by trained psychiatrists and/or psychologists at the different sites (see Fig. 1). Strategies aimed at optimizing the recruitment process will include the distribution of handouts or flyers to colleagues, physicians, and families, as well as an offer of reimbursement of study-related travel costs to participants. Furthermore, and depending on local regulations, information via presentations, websites, and social media campaigns will be provided. Regular calls will be made to patients to avoid participant withdrawal from the study.

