In the case that a participant’s psychological state deteriorates to a clinically significant degree during the trial, the investigators will either discuss with the participant the possibility of withdrawing from the study or decide that the participant should withdraw. If a participant, for any reason, requires treatment with certain therapeutic agents (i.e., antibiotics), the agent taken and time of administration will be noted. If any other protocol exclusion violation has occurred, the participant’s involvement will be discontinued. Participants may at any time request to be withdrawn from the study or revoke their consent to participate. If a patient is discontinued from the trial, a follow-up visit will be carried out to ensure the well-being of the participant.

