### Statistical analysis

Primary outcome measures will be analyzed by applying logistic regression analyses with type of treatment, diagnostic group (e.g., ADHD, BPD, or both), gender, and center as independent variables. A sample size of 180 participants will allow for detection of an odds ratio of 2.55 with 90% power, assuming a response rate of 20% for the CG at a significance level of 0.05. For simplification purposes, calculations will assume no effects of the covariates on the response rate. Secondary analyses will be performed on the secondary outcome measures assessed at the different time points. General linear models will be applied to examine effects of treatment group on continuous outcome variables while controlling for baseline assessment, gender, diagnostic group, and center. Categorical outcome measures will be investigated using generalized linear models. Treatment effects and their 95% confidence intervals will be reported. To investigate potential long-term effects of probiotics, data of the EG for 10 weeks will be analyzed. General linear models for repeated measurements will be applied to study changes from baseline to follow-up visit for this group, and missing data will be handled by the last observation carried forward method. Statistical significance will be defined at the 0.05 level.

Once the primary and secondary outcome measures results are obtained, all responsible investigators at all study sites will get access to the data to be able to reanalyze the data regarding specific additional research questions.

In case of an external request for replication, the respective statistical analysis will be provided by the trial statistician.

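### The abstract screens 180 participants while the methods recruit and power on 180; the target should be fixed as the number randomized, and the power figure has no allowance for missing week-10 responses

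*Protocol article*

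**What the plan says.** Three places in the protocol article give the number 180.

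- **Abstract, Methods/design:** the 180 are highly impulsive adults who have borderline personality disorder, ADHD or both. The text reads: "aged 18–65 years old, will be screened at three study centers".
- **Study population and recruitment:** "A total of 180 participants (60 subjects per site) will be recruited".
- **Statistical analysis:** "A sample size of 180 participants will allow for detection of an odds ratio of 2.55 with 90% power". The calculation takes 20% response among controls and alpha 0.05, and the covariates are taken to have no effect on response.

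Other sections bear on which 180 is meant. Randomization and study intervention randomizes 1:1, and only those found eligible. The screening visit (Participant timeline, Table 3) includes the severity scores, the diagnostic interviews and the eligibility check. Table 1 lists nine exclusions.

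Loss after randomization is also foreseen. Participants may be discontinued after an adverse event, may leave after clinical deterioration, and may withdraw at any time. The article adds: "If any other protocol exclusion violation has occurred, the participant’s involvement will be discontinued". Regular calls are planned to prevent withdrawal. No screen-failure or dropout rate is given.

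**The concern.** Screened, recruited and powered are three stages of one participant flow. They share one count only if nobody fails screening and nobody lacks an outcome. With the thresholds and exclusions listed, some screen failures are to be expected, so the abstract and the methods cannot both be literally right.

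Two things are at stake. One is clarity about the target: a reader of the abstract and a reader of the methods would expect different numbers randomized. The other is the power figure. The number to be recruited is exactly the number in the power statement, so the plan holds nothing back for participants without a response at T2 (week 10). This remains after the 90% is corrected, and the two shortfalls add up.

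**Working it through.** **1. The number 180, stage by stage**

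| Stage | What the article gives |
|---|---|
| Screened | 180 (abstract) |
| Recruited | 180, 60 per site (Study population and recruitment) |
| Randomized | no separate number; only eligible participants |
| Behind the power | 180 (Statistical analysis) |
| With a T2 response | no number |

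The word *recruited* does not fully settle the matter. Recruitment is said to have begun on 22 February 2019. Trial status gives that date as the first consent and 27 February 2019 as the first randomization. Recruitment thus appears to be counted from consent, which Table 3 places at the screening visit. This is suggestive, not conclusive.

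**2. Inputs for the power check**

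- Control response p1 = 0.20, odds ratio 2.55, alpha 0.05, N = 180 (Statistical analysis).
- Allocation 1:1, so n = 90 per arm.
- No covariate effects, so a comparison of two proportions applies.
- Sidedness is not stated. Two-sided is taken, in line with "Treatment effects and their 95% confidence intervals will be reported".

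Experimental response: control odds 0.20/0.80 = 0.25; 0.25 × 2.55 = 0.6375; p2 = 0.6375/1.6375 = 0.3893.

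**3. The stated 90%**

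Power = Φ[ ((p2 − p1)√n − 1.960·s0) / s1 ], where

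- mean response = (0.20 + 0.3893)/2 = 0.2947
- s0 = √(2 × 0.2947 × 0.7053) = 0.6447
- s1 = √(0.20 × 0.80 + 0.3893 × 0.6107) = 0.6307

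At n = 90: (0.1893 × 9.487 − 1.960 × 0.6447)/0.6307 = (1.796 − 1.264)/0.6307 = 0.844, so power is **80.1%**.

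Other versions with 180 in total also miss 90%: 81.3% with unpooled variance and 78.4% with a Wald test on the log odds ratio. One-sided 0.05, which nothing in the article supports, gives 87.8% pooled and 88.5% unpooled. In reverse, the odds ratio detectable with 180 at 80% power is 2.548, against the stated 2.55; at 90% power it is 2.91. Two-sided 90% power would need 240 participants with an outcome. The pair 180 and 2.55 is therefore an 80% calculation with every participant contributing.

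**4. Effect of loss**

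The loss rates are assumptions. Participants without a T2 response are taken as not analysed, and loss as equal in both arms.

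| Assumed loss | With outcome | Calculation | Power |
|---|---|---|---|
| 0% | 180 | (1.796 − 1.264)/0.6307 = 0.844 | 80.1% |
| 10% | 162 | (1.704 − 1.264)/0.6307 = 0.698 | 75.7% |
| 20% | 144 | (1.606 − 1.264)/0.6307 = 0.543 | 70.7% |

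**5. If those lost are counted as non-responders instead**

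N stays at 180, but if 20% and 38.9% describe participants who were observed, both rates shrink. At an assumed 10% loss they become 0.20 × 0.90 = 0.180 and 0.3893 × 0.90 = 0.350. Then s0 = 0.6243, s1 = 0.6125, and (0.1704 × 9.487 − 1.960 × 0.6243)/0.6125 = 0.641, giving 73.9%. If the 20% and the odds ratio already count those lost as non-responders, power stays at 80.1%.

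**The case against.** The strongest reply is that this is one loose verb in an abstract. The two methods sections agree on 180, and the abstract describes its 180 as already highly impulsive and diagnosed, which is established at screening. That reading is the most natural one, and I adopt it. A reader might infer from the abstract that recruitment stops once 180 have been screened, and that the randomized sample will fall well short. The documents do not support this: no such stopping rule is stated, and the target of 60 per site points the other way.

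A reader might also infer that the trial will not have the sample size on which its power rests. That does not follow either. The power statement speaks of a sample size, not of a number analysed, and if 180 are randomized and all are kept in the analysis, the analysed number can be 180.

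A further reply is that handling of dropouts is commonly left to the full protocol or analysis plan, which are not shown. That is fair, and the absence of such a rule is not the complaint. Last observation carried forward could keep some participants in. However, the article mentions it with the repeated-measures models for the experimental group, and the improvement rating, one half of the response definition, is first taken at week 5. A participant who leaves before then has no rating to carry forward.

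Finally, the loss rates are not in the documents, and screen failure and dropout are different losses. Both points stand. The figures under loss are therefore illustrations, and they concern missing T2 responses only. What survives is the mismatch in wording and the fact that the stated inputs give about 80% before any loss.

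**Conclusion.** The point holds as a minor correction of wording and of the power statement. The abstract contradicts the methods on what 180 counts; 180 is best read as the number to be randomized. On the stated inputs with a two-sided 0.05 test, power is at most about 80% (78% to 81% depending on the formula), and that requires all 180 to contribute an outcome. Any loss that leaves participants out lowers it, to about 76% at 10% and 71% at 20%. Those two figures rest on assumed loss, equal between arms, and on analysis of observed T2 responses only. The true shortfall is unknown because no loss rate is given.

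**What to change.** Make these changes together with the correction of the 90% figure.

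- **Abstract, Methods/design:** replace *screened* with *randomized*.
- **Study population and recruitment:** state that 180 (60 per site) is the number randomized.
- **Statistical analysis:** state that the power figure applies to 180 participants with a primary outcome, and restate it as about 80% for an odds ratio of 2.55 (two-sided 0.05). Add the lower figure under the sponsor's own expected loss, labelled as an assumption.

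Do not increase enrolment on this account. The cost is a few sentences and a less favourable power statement; no participants, visits or analyses are added.

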**Discussion:**

This is the first randomized controlled trial to determine the effects of supplementation with synbiotics on reducing impulsive and compulsive behavior. This clinical trial can contribute to explaining the mechanisms involved in the crosstalk between the intestinal microbiome and the brain. If effects can be established by reducing impulsive and compulsive behavior, new cost-effective treatments might become available to these patients.

**Trial registration:**

ClinicalTrials.gov, NCT03495375. Registered on 26 February 2018.

## Background

Impulsivity may be defined as “a predisposition towards rapid, unplanned reactions to internal or external stimuli, with diminished regard to the negative consequences that such reactions may have for the impulsive individual or others” [1–4]. In contrast, compulsivity represents “the performance of repetitive and functionally impairing overt or covert behavior without an adaptive function, performed in a habitual or stereotyped fashion, either according to rigid rules or as a means of avoiding perceived negative consequences” [2, 5]. Both traits share neuronal mechanisms involving a dysfunctional inhibition of thoughts and behavior [1, 6], and, rather than unitary phenomena, they are considered as multidimensional constructs that involve disruption within a range of neural processes, including attention, perception, and coordination of motor and/or cognitive processes. Impulsive and compulsive symptoms are overrepresented in individuals with several psychiatric disorders, such as attention-deficit/hyperactivity disorder (ADHD), borderline personality disorder (BPD), and/or obsessive-compulsive disorder [7]. Importantly, maladaptive impulsivity and compulsivity can lead to serious consequences not only for affected individuals and their families but also for society. They predispose individuals to aggressive or addictive behaviors, increasing the risk for mortality [8]. Despite this, data about modifiable risk and protective factors are largely lacking.

### Nutrition, brain, and behavior

Not only heritability, sex, and socioeconomic status (SES) but also diet may play a pivotal role in impulsive and compulsive symptomatology [9, 10]. In line with this, a number of studies have shown that different nutrient combinations may have interactive effects on cognitive function and behavior, including antioxidants; omega-3 polyunsaturated fatty acids (PUFAs); monounsaturated fatty acids; polyphenols; potassium; calcium; zinc; fiber; folate; and/or vitamins A, B_12_, C, D, or E [11–13]. More specifically, recent reports have linked aggressive behavior with low blood omega-3 PUFA levels and/or with low seafood consumption [14], and several animal studies have found that the long-term consumption of a low-calorie diet enhances autophagy and protects neurons effectively against aging, maintaining learning and memory capacity, whereas long-term consumption of a high-calorie diet facilitates neuronal loss in the hippocampus, aggravating age-related cognitive impairments [15, 16].

Importantly, the type of food intake can influence brain development and function in all age groups, with a recent study showing that prenatal exposure to an unhealthy diet was associated with ADHD symptoms, further linked to altered epigenetic modification of blood-derived DNA [17, 18]. However, these findings have not been consistently replicated in large-sample randomized controlled trials (RCTs), and the underlying mechanisms remain unknown [19–23].

### Gut microbiome, microbiota, and behavior

Although *microbiota* refers to the specific microorganisms that are found within a specific environment, *microbiome* refers to the collection of genomes from all the microorganisms found in this particular environment [24]. It is hypothesized that an imbalance in the gut microbiota (dysbiosis) may have a negative effect on neurodevelopment, behavior, and cognition [25–31]. Related to this, changes in human microbiome and/or microbiota composition have been consistently found in individuals with autism spectrum disorder (ASD) [32–36], and a pilot study on the microbiome has demonstrated, for the first time, a difference in several bacterial taxa between subjects with ADHD and healthy control subjects [37]. Specifically, lower *Firmicutes* genus and higher *Bifidobacterium* genus were found in subjects with ADHD than in healthy individuals, with the increase in the *Bifidobacterium* genus relating to decreased ventral striatal functional magnetic resonance imagining responses during reward anticipation [37].

The relationship between gut microbiota and the brain seems to be bidirectional. The gut microbiota modulates brain function and development, and the brain can alter the gut microbiota, allowing colonization by pathogenic bacteria [38–40]. Illustrating this idea, some studies have shown an overrepresentation of gastrointestinal symptoms in patients with both neurodevelopmental and neuropsychiatric disorders [41–48], and a study in healthy students found that during exams, psychological stress increased at the same time that numbers of lactobacilli in stool samples decreased [49].

But how does this bidirectional communication—the gut–brain axis—work? The “enteric nervous system” is complex and, regarding neurotransmitters and signaling molecules, similar to the brain [50]. As an example, 95% of all circulating serotonin, dopamine, or noradrenaline precursors are produced by our gut microbiota [50]. This system is connected to the central nervous system through hormonal or innate neuronal pathways [51] that are critical for its development and vice versa [52]. Furthermore, studies have shown that the gut flora is critically involved in immunoregulation [53–55], whereas some reports have shown the immune system as an important regulator of neurodevelopment and synaptic function in the brain [56]. In line with this, immune dysfunction and/or autoimmunity have been speculated to be associated with many neuropsychiatric and neurodevelopmental disorders, such as ADHD [57, 58]. Supporting this idea, an increased incidence of immune-mediated disorders (e.g., asthma, allergic rhinitis, atopic dermatitis, allergic conjunctivitis, psoriasis, thyrotoxicosis, or type 1 diabetes) has been found among patients with ADHD [59–62]. Moreover, elevated inflammatory markers (especially interleukin [IL]-6) [63–65] or autoantibody levels (e.g., anti–basal ganglia antibodies, antibodies against the dopamine transporter) [66, 67] have been found both in serum/plasma and in cerebrospinal fluid of these patients [63, 68, 69].

### Probiotic/synbiotic interventions

Probiotic bacteria, or “probiotics,” are live, nonpathogenic microorganisms that normally inhabit the intestines and contribute to the health of the host by improving microbial balance [70]. On the other hand, prebiotics are nondigestible ingredients that selectively stimulate the growth and activity of these probiotic microorganisms [71]. The synergic combination of probiotics and prebiotics is referred to as *synbiotics*. Recent findings suggest that probiotics and/or synbiotics can not only revert dysbiosis but also modulate brain activity and improve cognition, mood, and behavior [72–78]. Importantly, a recent study has shown that oral administration with *Lactobacillus* during the first 6 months of life reduced the prevalence of ADHD or ASD at the age of 13 [79]. However, the exact mechanisms by which probiotics and/or synbiotics exert their action remain unknown. Recent findings suggest immunomodulatory and anti-inflammatory properties of these agents [80], possibly by selectively targeting T-helper (Th) type 1 [81] and Th17 cell lineages [82].

The aim of the present multicenter, prospective, double-blind, placebo-controlled, parallel-group study is to investigate the effect of a synbiotic formula (Synbiotic 2000 Forte 400; Synbiotic AB, Höganäs, Sweden) on reducing impulsive, compulsive, and aggressive behaviors in a sample of highly impulsive adults with a diagnosis of attention-deficit/hyperactivity disorder (ADHD) and/or borderline personality disorder (BPD). In this study, we will test the idea that supplementation with probiotics will, by modifying the gut microbiota structure and metabolism, reduce impulsive, compulsive, and aggressive behaviors in this specific population and thereby improve their daily life function. Moreover, we will evaluate the composition of gut microbiota in this population and link it to inflammatory/immunological abnormalities that can underlie core symptoms of these disorders.

## Methods/design

This protocol is presented in accordance with the 2013 SPIRIT (Standard Protocol Items: Recommendations for Interventional Trials) Statement (See Additional file 1 for the populated SPIRIT Checklist (83).

### Trial design and study setting

The Treatment of impulsivity in adults with probiotics (PROBIA) trial is designed as a 10-week multicenter, prospective, randomized, double-blind, placebo-controlled, parallel design study. It will be performed in close cooperation between three European clinical centers: Goethe University Hospital Frankfurt (Department of Psychiatry, Psychosomatic Medicine and Psychotherapy), Frankfurt, Germany; Vall d’Hebron Research Institute (Psychiatry, Mental Health and Addictions Group), Barcelona, Spain; and Semmelweis University (Department of Psychiatry and Psychotherapy), Budapest, Hungary. These centers are all affiliated with or part of university hospitals and, with around 300 new inpatients and outpatients visiting each center every year, are considered as reference centers for the treatment of ADHD, BPD, and other disorders characterized by high impulsivity levels.

### Study population and recruitment

Participants will be eligible for participation in this study if they meet all the inclusion criteria and none of the exclusion criteria listed in Table 1. With the aim of gender balancing the study, at least 30% female participants will be included.

**Table 1 Tab1:** Inclusion and exclusion criteria of the PROBIA trial

Inclusion criteria	Both males and females aged 18–65 years
	A high level of multidimensional impulsivity based on both a Clinical Global Impression–Severity Scale (CGI-S) score ≥ 4 and an Affective Reactivity Index (ARI) ≥ 5
	DSM-5 criteria for attention deficit/hyperactivity disorder (ADHD) and/or borderline personality disorder (BPD) confirmed by a structured diagnostic interview (ADHD: Diagnostic Interview for Adult ADHD [DIVA 2.0]; BPD: Structured Clinical Interview for DSM-IV [SCID-II])
	Deemed reliable and compliant with the protocol by the investigator
	Ability to speak and comprehend the native language of the country in which the assessments take place
	Informed consent signed
Exclusion criteria	Antibiotherapy within the last 6 weeks prior to study
	Currently taking probiotics
	Presence of a major psychiatric disorder with psychotic symptoms or other major psychiatric conditions requiring hospitalization (e.g., significant mood disorders)
	Neurological disorders involving central functions (e.g., epilepsy, multiple sclerosis, narcolepsy)
	Intelligence quotient (IQ) < 70 (measured by WAIS, if available)
	Major physical illnesses of the cardiovascular, endocrine, pulmonal, immune, or gastrointestinal system or undergoing immunosuppression
	History of/present clinically relevant somatic acute or chronic disorders that, in the opinion of the investigator, might confound the results of tolerability/safety assessments or prohibit the patient from completing the study or would not be in the best interest of the patient
	Documented allergy, hypersensitivity, or intolerance to any of the ingredients of the intervention
	Subject has taken another investigational product or taken part in a clinical study within 30 days prior to entering the study.

*Abbreviations: DSM Diagnostic and Statistical Manual of Mental Disorders*, *PROBIA* Treatment of impulsivity in adults with probiotics, *WAIS* Wechsler Adult Intelligence Scale

Recruitment began on 22 February 2019 and will have a duration of 2 years. A total of 180 participants (60 subjects per site) will be recruited by trained psychiatrists and/or psychologists at the different sites (see Fig. 1). Strategies aimed at optimizing the recruitment process will include the distribution of handouts or flyers to colleagues, physicians, and families, as well as an offer of reimbursement of study-related travel costs to participants. Furthermore, and depending on local regulations, information via presentations, websites, and social media campaigns will be provided. Regular calls will be made to patients to avoid participant withdrawal from the study.

